
### Why investigate RIPC in patients with an unruptured intracranial aneurysm?

Treatment of unruptured intracranial aneurysms under general anesthesia is a highly standardized clinical situation. In this situation, (1) the incidence of clinically silent ischemia is high (as high as 60 % in patients undergoing endovascular procedures [1, 74]), (2) no previous ischemic damage has occurred (and a baseline for biomarker determination can be established beforehand), and (3) the preconditioning stimulus can be administered at a pre-specified moment prior to occurrence of the real damage. Aneurysm treatment may therefore present some essential features needed to study the induction of ischemic tolerance in the brain under clinical conditions despite all problems associated with the determination of valid study endpoints [37, 45, 75, 76].

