#### Statistical analysis

Statistical analysis will be performed by an independent external statistician ([name]). This study is designed as an explorative study to provide data for future confirmatory studies. The main outcome variable (area under the curve, AUC) for each biomarker will be analyzed using intra-operative ischemia as the only explanatory variable in the two groups. No corrections will be made for multiplicity. A difference of ≥ 2 standard deviations (SD) in the main outcome variable is considered to be a statistically relevant effect. The alpha level is set at 0.05 %. The 95 % confidence intervals for the differences will be calculated.

No a priori empirical evidence suggests which of the six chosen biomarkers would be the ideal single primary outcome, but to define the sample size, we allocated the AUC of S100 as the primary outcome. Power analysis aiming to detect a difference of more than two SD in the primary outcome between the groups would require a sample size of *n* = 16σ2/d2 for a two-sided α = 0.05 and 1-β = 0.8 [85]. *N* = 4 patients per group would permit a difference of ≥ 2 SD in serum biomarker levels to be detected in the study population. Assuming that only one in five patients will sustain cerebral ischemia during aneurysm treatment, this would require a sample of *n* = 20 patients per group. Additional 20 % (*n* = 4 patients) per group will be included for unexpected dropouts, unexpected low rates of intra-interventional ischemia or unexpected loss to follow-up. This would require a total study population of *n* = 48 patients (*n* = 24 per group).

All statistical analysis will be performed on an intention-to-treat basis and per protocol. Standard methods of exploratory data analysis will be used for group comparison. Quantitative parameters will be tested for normality and compared using the *t* test or compared with the Mann–Whitney *U* test for non-normally distributed data. Qualitative parameters will be compared using the chi-squared test or Fisher’s test. Group differences for the main outcome variable will be compared using the two-sided *t* test for independent groups or the Mann–Whitney *U* test, as appropriate. Secondary outcome parameters will be compared using the Mann–Whitney *U* test for quantitative data and the chi-squared or Fisher's test for dichotomized outcome data.

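### Multiplying n by 5 for a one-in-five ischemia rate does not fit the all-patient intention-to-treat comparison: 24 per group has about 27 % power or less at that rate, not the implied 80 %

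*Protocol article*

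**What the plan says.** All of this is in the Statistical analysis section of the protocol article unless noted.

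- **Base figure.** The AUC of S100 is taken as the primary outcome for sizing. "Power analysis aiming to detect a difference of more than two SD in the primary outcome between the groups would require a sample size of" "16σ2/d2 for a two-sided α = 0.05 and 1-β = 0.8". Four patients per group are said to permit a "difference of ≥ 2 SD in serum biomarker levels to be detected in the study population".
- **Ischemia adjustment.** "Assuming that only one in five patients will sustain cerebral ischemia during aneurysm treatment, this would require a sample of" 20 per group. A further 20 % (4 per group) covers dropout, a low ischemia rate and loss to follow-up, giving 24 per group and 48 in all.
- **Primary test.** "Group differences for the main outcome variable will be compared using the two-sided" t test for independent groups, or the Mann–Whitney test.
- **Analysis population.** "All statistical analysis will be performed on an intention-to-treat basis and per protocol". Neither set is limited to patients with ischemia.
- **Role of ischemia.** An earlier sentence in the section says the AUC of each biomarker will be analysed in the two groups with intra-operative ischemia as its sole explanatory variable. It names no model, interaction or subset.
- **Ischemia rate elsewhere.** The Background section on why unruptured aneurysms are studied gives an incidence of clinically silent ischemia "as high as 60 % in patients undergoing endovascular procedures".

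**The concern.** Dividing n by the share of affected patients is right when only affected patients are compared. When everyone randomised is compared, the unaffected patients stay in both groups and pull the mean difference towards zero. The required n then grows with the square of the dilution, 1/0.2² = 25, rather than with 1/0.2 = 5. This holds whatever the base figure is, so it is separate from whether 4 per group is itself right.

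At stake is the operating characteristic that readers will attach to the trial. The sizing suggests that a 2 SD effect in ischemic patients would be found four times in five at the assumed ischemia rate. With the stated test it would be missed about three times in four, or more often. The adequacy of 24 per group therefore depends heavily on the ischemia rate, and the text does not show this.

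**Working it through.** **Inputs.** From Statistical analysis: two-sided α = 0.05, power 0.80, effect 2 SD, ischemia rate 0.20, 20 % reserve. From Randomization: 1:1 allocation. The same section also prints "The alpha level is set at 0.05" followed by a percent sign. I take α as 0.05, because the sample-size sentence and the 95 % intervals use it; that wording is a separate matter. I assume, as the plan's own multiplication implies, that the 2 SD effect applies to ischemic patients and that non-ischemic patients show none.

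**1. The plan's figure reproduces.** 16σ²/d² with d = 2σ: 16/4 = 4. 4/0.20 = 20. 20 × 1.2 = 24 per group, 48 in total.

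**2. Whole-group effect.** 0.20 × 2 SD + 0.80 × 0 = 0.4 SD.

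**3. Required n by the plan's formula.** 16/0.4² = 100 per group before any reserve. The t test has 80.4 % power at 100 per group.

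**4. Power of the stated t test, common SD (noncentral t).**

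| n per group | Ischemia rate | Whole-group difference | Power |
|---|---|---|---|
| 20 | 20 % | 0.4 SD | 23 % |
| 24 | 20 % | 0.4 SD | 27 % |
| 24 | 40 % | 0.8 SD | 77 % |
| 24 | 60 % | 1.2 SD | 98 % |

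**5. Allowing for the mixture.** If 2 SD is measured in units of the SD within ischemic (or non-ischemic) patients, mixing the two kinds of patient widens the groups. Suppose ischemia adds 2 SD and RIPC removes all of it. The control variance is then 1 + 0.2 × 0.8 × 2² = 1.64, and the average over the arms is (1 + 1.64)/2 = 1.32. The standardised difference is 0.4/√1.32 = 0.35, and power at 24 per group is 22 % by formula and 21 % by simulation. At ischemia rates of 40 % and 60 % the same simulation gives about 61 % and 92 %. If ischemia adds 3 SD and RIPC removes 2 of them, power at a 20 % rate falls to about 15 %; if it adds 4 SD, to about 11–12 %.

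**6. What 24 per group can detect.** 80 % power needs a whole-group difference of 0.83 SD. The 95 % confidence interval half-width is 2.013 × √(2/24) = 0.58 SD. With 2 SD in ischemic patients, 0.83 SD corresponds to an ischemia rate of 0.83/2 = about 41 % on a common SD. With the mixture of step 5 it is about 50 % (79 % power at that rate).

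**7. Ischemia-based readings, 20 % rate (simulation).** A t test in ischemic patients only averages about 55 % power at 20 per group and 67 % at 24. One reason is that the count of ischemic patients varies: the chance that both arms reach 4 is 0.589² = 35 % at 20 per group and 0.736² = 54 % at 24. A linear model with a group-by-ischemia interaction, which borrows the residual SD from all patients, reaches about 70 % and 79 %.

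**The case against.** The strongest reply rests on the sentence that makes intra-operative ischemia the sole explanatory variable. It suggests why the factor of 5 was chosen: the authors wanted about 4 ischemic patients per arm. On that view the arithmetic is sound, and with an interaction model the planned n comes close to 80 %. This stands as an account of intent, and the individual sums (4, 20, 24) are correct. It does not settle the matter. The sentence defines no subset or model, while the comparison spelled out for the main outcome is by group under intention to treat. The 79 % needs a model that the article does not state and uses the whole reserve. Intra-procedural ischemia also arises after randomisation and could be influenced by RIPC, so conditioning on it gives up the protection of randomisation. That last point concerns bias rather than power.

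A second reply is that the trial is exploratory, warns in its Discussion that it may prove underpowered, and already plans confidence intervals. This lowers the weight of the point. The warning is about small biomarker effects, though, and does not tell the reader that the very large assumed effect would usually be missed.

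Three stronger readings are tempting and are not supported:

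- That the article expressly claims 80 % power for 20 or 24 per group. It attaches 80 % to the formula and the base figure of 4; for 20 and 24 it is only implied.
- That a null result would be taken as evidence against RIPC. The Discussion says that planning after a null result will rest on the full clinical, imaging and neuropsychological results, and that the trial will give no definitive answer.
- That power is poor at any plausible ischemia rate. At the 60 % quoted in the Background it is about 92–98 % under the assumptions of steps 4 and 5.

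**Conclusion.** The concern holds as a mismatch between the sizing and the stated test. At the assumed one-in-five rate, the intention-to-treat comparison with 24 per group has about 27 % power (common SD) or about 15–21 % (within-stratum SD, ischemic excess of 2 to 3 SD of which RIPC removes 2), against an implied 80 %. The plan's own formula would need 100 per group. This rests on a 2 SD effect confined to ischemic patients, two-sided α of 0.05 and the by-group t test. The direction does not depend on the choice of SD or on the base figure of 4. Since the trial is exploratory and its size can be kept, this should be corrected in the text; it is not a case for enlarging the trial.

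**What to change.** 1. Keep the by-group intention-to-treat comparison as primary. Reconcile the ischemia sentence with it: either say that any ischemia-based analysis is secondary and name its model or subset, or remove the sentence.
2. Keep 24 per group, and replace the implied power for 20 and 24 per group with wording such as:

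> With 24 per group, the intention-to-treat comparison has 80 % power for a whole-group AUC difference of 0.83 SD (95 % CI half-width about 0.58 SD). If a 2 SD effect is confined to patients with ischemia, power is about 21–27 %, 61–77 % and 92–98 % at ischemia rates of 20 %, 40 % and 60 %. The lower figures use the within-stratum SD and assume that RIPC removes the whole 2 SD ischemic excess; the upper figures use a common SD. Power is lower still if the excess is larger.

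3. Report the observed rate of recorded intra-interventional ischemia per arm beside these figures. That is the quantity the sizing uses, and the Aneurysm treatment section already has possible ischemic events recorded. New MRI lesions are a different quantity and a secondary endpoint.
4. State that a non-significant AUC difference at an ischemia rate near 20 % is inconclusive.

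The cost is a rewritten sample-size paragraph and one line on interpretation. No patients are added and no procedure changes; the price is a less favourable stated power.

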### Why include two different procedures in the study protocol?

We included both procedures - microsurgical clipping and endovascular coil occlusion of intracranial aneurysms - because both may induce focal cerebral ischemia (ischemia to one defined cerebral vascular territory) and because both may lead to local endothelial damage. Both procedures carry a comparable risk to induce focal cerebral ischemia.

The difference is that, in endovascular procedures, the source of ischemia is inside the vessel and in direct contact with the endothelium and the bloodstream, whereas in microsurgical clipping, the ischemia-inducing agent is outside the vessel lumen. This might be a drawback in the study design but could also increase the external validity of this study. Other possible technical confounders in a study of this type that defeat standardization include but are not limited to (1) a different duration of vessel occlusion between the study individuals, (2) a lack of possibility to differentiate between complete and incomplete vessel occlusion, (3) the impossibility to control for collateralization of the occluded vascular territory, and (4) the fact that some patients will undergo repetitive occlusion periods and others a singular occlusive period as dictated by clinical necessity.

The goal of the RIPAT study is to investigate whether remote ischemic preconditioning during the elective treatment of intracranial aneurysms reduces the occurrence of ischemic damage as measured by serum biomarker determination, neuroimaging, and clinical, as well as neuropsychological, examination.

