## Discussion

This study uses the elective treatment of intracranial aneurysms as a paradigmatic situation to explore the neuroprotective effects of remote ischemic preconditioning. In this setting, ischemia as visualized by neuroimaging does occur, but is usually not clinically relevant. Nevertheless, serum biomarkers and/or advanced MRI techniques may be able to detect significant group differences between patients who underwent remote ischemic preconditioning and those who did not. In this case, any of these biomarkers may be a candidate as a secondary outcome parameter for future exploration in adequately powered phase III trials aimed at demonstrating a clinically relevant difference as the primary outcome. The primary outcome in such a trial could be the rate of cerebral events assessed within 30 days after randomization. These events comprise death or any new neurological deficit (whether temporary or permanent) attributable to an ischemic lesion detected by neuroimaging. We estimate that, in the setting of a multicenter study involving different institutions and different interventionalists, the rate of such events is 5 % in this patient population and that a reduction of this rate by 50 % would be clinically worthwhile.

In case any primary outcome parameter of the RIPAT trial does not show a statistically significant difference between the treatment and intervention group, the planning of future trials using ischemic preconditioning in this patient group will be based on the analysis of full results including all clinical, imaging, and neuropsychological data.

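### At the planning rate of one in five, chance variation in the number of ischemic patients uses up the whole reserve of four per group, so the stated margin for dropout or a lower ischemia rate does not exist

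*Protocol article*

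**What the plan says.** All of the sizing is in the Statistical analysis section of the protocol article.

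- The target is set by a "Power analysis aiming to detect a difference of more than two SD in the primary outcome between the groups", with the S100 AUC named as primary for sizing, "for a two-sided α = 0.05 and 1-β = 0.8". The formula given is n = 16σ²/d².
- From this, 4 "patients per group would permit a difference of ≥ 2 SD in serum biomarker levels to be detected in the study population".
- The next step is "Assuming that only one in five patients will sustain cerebral ischemia during aneurysm treatment, this would require a sample of" 20 per group.
- A further 20 %, that is 4 patients, "per group will be included for unexpected dropouts, unexpected low rates of intra-interventional ischemia or unexpected loss to follow-up". The total becomes 48, or 24 per group.

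Dividing 4 by one in five makes sense only if the 4 patients are ischemic patients. The same section also says that each biomarker's AUC will be analysed with intra-operative ischemia as the only explanatory variable in the two groups.

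**The concern.** Twenty is the group size at which the expected number of ischemic patients equals 4. The actual number varies from group to group, and power falls more when a group has too few than it rises when a group has too many. So 20 per group does not deliver the 80 % that exactly 4 and 4 would deliver, even if the assumed rate is right and nobody is lost. The plan treats 20 as sufficient and presents the next 4 as protection against unexpected events. If ordinary chance at the expected rate already needs those 4, nothing is left for the purposes named.

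What is at stake is how the result is read. The Discussion ties the planning of later trials to whether the primary outcome shows a significant difference. A null result would be read against a stated 80 % power with a cushion, when at the planning rate there is no cushion.

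**Working it through.** **Inputs from the Statistical analysis section.** Difference 2 SD; two-sided α = 0.05; power 0.80; 4 ischemic patients per group; ischemia rate 0.20 in both groups; 20 per group before and 24 after the reserve. The same section elsewhere gives alpha as 0.05 %, which conflicts with the sizing sentence. That is a separate matter, and 0.05 is used here.

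**Step 1: the plan's own figures.**
- n = 16σ²/d² with d = 2σ gives 16/4 = 4.
- Normal approximation at 4 and 4: Φ(2/√(1/4 + 1/4) − 1.96) = Φ(0.868) = 0.81.
- 4/0.20 = 20; 20 × 1.2 = 24; 2 × 24 = 48.

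The stated sizes reproduce.

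**Step 2: how often the expected 4 is reached.** For X ~ Bin(n, 0.20):
- n = 20: P(X ≥ 4) = 0.589; both groups 0.589² = 0.346.
- n = 24: P(X ≥ 4) = 0.736; both groups 0.736² = 0.542.

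These are probabilities of reaching a count. They are not power.

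**Step 3: power averaged over the random counts.** With a and b ischemic patients in the two groups,

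power = Σₐ Σ_b Bin(a; n, p₁) · Bin(b; n, p₂) · Φ(2/√(1/a + 1/b) − 1.96),

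where a group with no ischemic patient contributes zero. The t test column replaces Φ by the noncentral t probability with a + b − 2 degrees of freedom.

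| Evaluable per group | Ischemia rate (both groups) | Normal approximation | t test |
|---|---|---|---|
| 20 | 20 % | 72 % | 57 % |
| 24 | 20 % | 80 % | 68 % |
| 22 | 20 % | 76 % | 63 % |
| 19 | 20 % | 70 % | 54 % |
| 24 | 15 % | 66 % | 50 % |
| 24 | 30 % | 94 % | 89 % |

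The first two rows carry the point. Going from 20 to 24 lifts power from 72 % to 80 %, so the whole addition is needed to absorb chance at the assumed rate. The next three rows show what happens if anything is lost or the rate is lower. The row with 19 is for scale (24 × 0.8 = 19.2); the plan does not forecast a 20 % loss.

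The t test column is lower throughout, partly because the normal approximation is optimistic at such small counts: exactly 4 and 4 gives 66 % by t test. That gap is separate from the reserve.

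**Step 4: sensitivity to a lower rate under RIPC.** The document gives no effect of RIPC on the intra-operative ischemia rate. Purely as an assumption, 20 % in controls against 10 % with RIPC at 24 per group gives 61 % (46 % by t test).

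**The case against.** The strongest reply is that the plan asks for 80 % power and never asks for at least 4 ischemic patients in both groups with high probability. Missing 4 is not a cliff: by the normal approximation, counts of 3 and 5 give 78 % and counts of 3 and 6 give 81 %. This stands. A reader might take the 54 % from step 2 as the trial's power, or conclude that 24 per group fails to cover chance variation. The documents support neither: by the plan's own approximation 24 per group does give about 80 % at the planning rate. What remains is that it gives no more than that.

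A reader might also infer that the RIPC group is bound to fall short, because the goal is to learn whether "remote ischemic preconditioning during the elective treatment of intracranial aneurysms reduces the occurrence of ischemic damage". With a halved rate, both groups would reach 4 with probability 0.736 × 0.214 = 0.158. But the only halving in the article, "a reduction of this rate by 50 % would be clinically worthwhile", concerns clinical events in a possible later trial. Ischemic damage also differs from the vessel occlusions and pressure drops recorded during the procedure: a treatment that raises tolerance need not make those rarer. Equal rates are a defensible planning choice, so unequal rates belong in a labelled sensitivity case only.

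Nor does the text claim to absorb all three losses at full size at once; it joins them with 'or'. Loss to follow-up is a fair reason for extra patients where the 6- and 12-month secondary endpoints are concerned.

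Finally, one in five is cautious beside the figure of up to 60 % in the Background, the trial is labelled explorative, and the Discussion concedes that it may prove underpowered. At 30 % the difficulty is gone. But the reserve is offered partly against rates below the planning value, and that is exactly where it has nothing to give.

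**Conclusion.** The concern holds in a limited form. At a 20 % ischemia rate in both groups, power for 2 SD by the plan's approximation is about 72 % with 20 per group and reaches 80 % only with all 24 evaluable. The stated reserve is therefore consumed by chance variation, and any dropout or lower rate takes power below 80 %.

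This rests on three assumptions: that the 2 SD applies to a comparison among ischemic patients, which the division by one in five implies; that the counts are binomial and independent between groups; and that the planning rate is correct. It does not show that 48 patients is an unreasonable size for an exploratory trial. It shows that the size should not be described as carrying a margin at the planning rate.

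**What to change.** Keep 24 per group and restate the paragraph, for example:

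> At an ischemia rate of one in five in both groups, 24 evaluable patients per group give about 80 % power for a 2 SD difference among ischemic patients by the normal approximation (about 68 % by t test), allowing for random numbers of ischemic patients. The 4 additional patients per group are used up by this variation and leave no margin for dropout or a lower ischemia rate. Power is higher if the rate is higher (about 94 % at 30 %; 89 % by t test).

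A lower rate under RIPC may be added as a labelled sensitivity case (20 % against 10 %: about 61 %, or 46 % by t test). Loss to follow-up may stay as a consideration for the 6- and 12-month secondary endpoints, but not for the primary AUC, which is complete at day 5.

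The change is to wording only, with no added patients or procedures. Its cost is a less favourable stated figure.

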#### Randomization

The Center for Statistical Consulting and Continuing Education (CSCCE) at UMIT (University for Health Sciences, Medical Informatics and Technology) generated the random allocation sequence using the PLAN procedure in the SAS statistical package V.9.1. Participants were randomized 1:1 to either the preconditioning group or the sham group using block randomization with a block size of four at a time and a random-block sequence. Assignment of the study subjects was documented in a randomization schedule. Sequentially numbered sealed opaque envelopes containing group allocation for each patient were prepared using the random allocation sequence by a statistician not involved in patient treatment. Envelopes will be opened by one of the unblinded members of the study group (see above) after induction of anesthesia.

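### Choosing the t test or Mann–Whitney test for the primary AUC by a normality check favours the rank test as a benefit confined to a minority of patients grows; the cost is small at 2 SD and large only under bigger shifts or skewed markers with partial protection

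*Protocol article*

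**What the plan says.** All of this stands in the Statistical analysis section of the protocol article.

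- General rule: "Quantitative parameters will be tested for normality and compared using the" t test, or the Mann–Whitney test where the data are not normal.
- Main outcome, the AUC of each biomarker: "Group differences for the main outcome variable will be compared using the two-sided" t test or the Mann–Whitney test, whichever is judged appropriate. No normality test, level, unit of testing (per arm, residuals or pooled) or default is named.
- Quantitative secondary outcomes get the Mann–Whitney test with no such choice, so the primary outcome is less firmly fixed than the secondary ones.
- A relevant effect is at least 2 SD, and 95% confidence intervals for the differences are promised. The sample size comes from a formula for a difference in means: "Power analysis aiming to detect a difference of more than two SD in the primary outcome between the groups".
- The expected share of patients affected is stated: "Assuming that only one in five patients will sustain cerebral ischemia during aneurysm treatment".
- Analyses are to be run both by intention to treat and per protocol, for six biomarkers.

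**The concern.** If about a fifth of sham patients have a raised AUC and fewer RIPC patients do, the benefit lies in the right tail of one arm. That tail is what a normality test detects. Once it is detected, the rule moves to a rank test, which gives a tail of 20% the same ranks whether the values are moderately or greatly raised. So the rule can lose power as the true benefit grows.

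The reported effect may also change in kind. The plan defines its effect and its sample size on the mean scale, and the rank test does not estimate a difference in means. One biomarker could be reported by a difference in means and another by a rank comparison, and one biomarker could differ between the two analysis sets. The trial is meant to supply data for planning a phase III trial, which needs effect estimates that can be compared across markers.

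**Working it through.** **Plan's own figure.** n = 16σ²/d² with d = 2σ gives 16/4 = 4 per group. Then 4 × 5 = 20, and 20 × 1.2 = 24 per group, 48 in total. This reproduces.

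**Inputs from the plan.** 1:1 allocation, 24 per group, 20% affected, 2 SD in AUC, two-sided 0.05. The section also says "The alpha level is set at 0.05" followed by a per cent sign, which conflicts with "for a two-sided α = 0.05 and 1-β = 0.8"; 0.05 is used here. The comparison simulated is between the randomized groups.

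**Assumptions, not in the plan.** The distribution of the AUC (normal, or lognormal with log-SD 0.4 or 0.5), shifts other than 2 SD, the degree of protection, and the normality test. Four gates at the 0.05 level were compared: Shapiro–Wilk per arm, on residuals and pooled, and Lilliefors on residuals. Relative loss = 1 − power(rule)/power(t test).

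**Normal markers, full protection, 24 per group** (4,000–8,000 runs; ranges are over the four gates):

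| Shift in affected sham patients | t test | Mann–Whitney | Normality rejected | Planned rule | Relative loss |
|---|---|---|---|---|---|
| 2 SD | 21.1% | 17.0% | 7–16% | 19.8–21.0% | 1–6% |
| 4 SD | 41.4% | 21.4% | 41–90% | 22.1–33.9% | 18–47% |
| 6 SD | 52.1% | 20.8% | 88–99% | 20.8–24.3% | 53–60% |

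Example at 4 SD with Shapiro–Wilk per arm: 1 − 26.4/41.4 = 36%. At 3 SD, separate runs with the per-arm gate give 27 v 31%: 1 − 27/31 = 13%.

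With 20 per group the losses are 0–4% at 2 SD, 11–42% at 4 SD and 42–59% at 6 SD. With the affected share fixed rather than random (24 per group, residual gate), they are 1%, 16%, 41% and 69% at 2, 3, 4 and 6 SD.

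**Direction.** In a further run with the per-arm gate, as the shift grows from 3 to 6 SD, t-test power rises from 33% to 53% while power under the planned rule falls from 29% to 22%.

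**Lognormal markers, full protection, shift measured on the AUC scale, 24 per group.**
- 2 SD, log-SD 0.4: normality is rejected in about 69% of trials, yet power is 19.9 v 21.3%, a loss of 1 − 19.9/21.3 = 7%. A second run gives 19 v 22%, about 13%. With log-SD 0.5 the loss is 14–16%.
- 3 SD, log-SD 0.4: 23 v 33%, a loss of 1 − 23/33 = 30%.
- 4 SD, log-SD 0.4: 22 v 41%, a loss of 1 − 22/41 = 46%.

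**Partial protection** (affected RIPC patients raised by 2 SD, affected sham patients by 4 SD). Normal markers: loss 15–43%, from a t-test power of only 11.3%. In the lognormal runs with partial protection: loss 40–48%.

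**Type I error** of the two-stage rule: 4.4–5.6% across all runs.

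**Dilution.** 2 SD in 20% of patients is a mean difference of 0.2 × 2 = 0.4 SD. That is why even the unconditional t test has about 21% power at 24 per group, against the planned 80%.

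**Alternative.** Log AUC adjusted for log baseline (assumed baseline correlation 0.5) against the planned rule: 22 v 21% at 2 SD normal, 40 v 26% at 4 SD normal, 36 v 23% at 4 SD lognormal, with type I error near 5%.

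**The case against.** The strongest reply is that in the scenario the plan actually describes, the rule does little harm. That stands. A reader might infer that one in five affected at 2 SD is routinely sent to the rank test and loses a third or more of its power. The documents do not support this: with normal markers the gate fires in 7–16% of trials and costs almost nothing, and with lognormal markers it fires often but costs 7–16%. If only ischemic patients were compared (4 v 4, 2 SD), normality is rejected in at most 10% of trials, and even using the Mann–Whitney test throughout costs 25% (49 v 65%).

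A reader who adds the shift on the log scale will find larger losses at a nominal 2 SD (18 v 26%). With log-SD 0.4, however, that shift is about 2.9 SD in AUC, and the plan states its effect in SDs of the AUC.

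Nor should the low power at 2 SD be blamed on the choice of test, since dilution explains most of it.

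Other replies stand in part. The gate is unnamed, so the size of the loss depends on a choice the reviewer must supply, and an SAP not shown here may settle it. The article nevertheless states the data-driven rule itself. A location-shift interval can accompany the Mann–Whitney test, so an interval would still be available, but it would not estimate the same quantity as a difference in means. The trial is exploratory, which lowers the weight of the point without removing the need for comparable estimates.

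**Conclusion.** The point holds in a limited form. The primary test is chosen from the data, and when benefit is confined to a minority the choice moves toward the less sensitive test as the benefit grows. The reported effect measure can also vary between biomarkers and analysis sets.

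At the plan's minimum effect the relative loss is about 0–6% (normal) or 7–16% (lognormal). A loss of about a third to more than a half needs AUC shifts of about 3–4 SD or more, or skewed markers with partial protection. The plan gives 2 SD as a minimum, so larger shifts are not excluded, but it states none and gives no distribution for the AUC. Type I error is not materially affected.

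**What to change.** Remove the normality test as a gate. Before unblinding, prespecify one analysis for every biomarker and both analysis sets: the between-group difference in mean log AUC, adjusted for the log of the baseline value already collected, reported as a ratio of geometric means with a 95% CI, whatever the observed distribution. Keep the Mann–Whitney test as a sensitivity analysis.

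The cost is wording only; no extra sample or visit is needed. There are three downsides. Results are on a ratio scale. Values below the detection limit need a rule. The log scale gives up some power to the raw-scale t test when shifts are large: in unadjusted runs 48 v 53% at 6 SD with normal markers, and 30 v 41% at 4 SD with lognormal markers.

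Part of the gain comes from the baseline adjustment. Without it, at 2 SD with lognormal markers, the log-scale t test (18.6%) was no better than the planned rule (19.9%). The change does not cure the dilution, which needs separate attention in the sample-size section.
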